### Concealment mechanism {16b}

Opaque sealed envelopes will be made by a third party not related to the study and stored at the Goulburn Valley Health Obstetrics and Gynaecology Department. The envelopes will be not accessible to individuals directly involved in the study.

### Implementation {16c}

A third party, not involved in the assignment or care of the trial participants, will generate the permuted blocks for randomisation and place the assigned treatments in the sealed envelopes. Study investigators will lead participant recruitment, informing participants of all the trial procedures and obtaining their informed consent before the initial inclusion in the study. Study investigators will confirm the eligibility of the participant prior to any study procedures being undertaken. Prior to CS delivery, participants will pick one of the opaque sealed envelopes at random and pass it on to the treating team. Upon opening of the envelope, which designates chlorhexidine or 1% povidone iodine or no vaginal cleansing, the treating team will administer the allocation immediately prior to CS.

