### Trial design {8}

This will be a single-centre, three-arm, single-blind, randomised controlled trial. A total of 396 eligible patients will be randomised in a 1:1:1 ratio to receive pre-operative vaginal cleansing with 1% povidone iodine or chlorhexidine or no toileting (control) immediately prior to CS.

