### Sample size {14}

We assume that the interventions will improve the rate of infection including post-operative infective complications (within 28 days post-CS) by 50% compared to the control. Thus, for sample size estimation in this study, we set *P*_1_ = 8% (as per overall prevalence of post-CS infection range 3–15%), *P*_2_ = 4%, significance level = 5% and the study power = 80%.

Therefore,
$$ n\ge {\left(\frac{Z_{\alpha }+{Z}_{\beta }}{\mathrm{ES}}\right)}^2 $$$$ \mathrm{ES}=\frac{P_1-{P}_2}{\sqrt{P_1\left(1-{P}_1\right)}} $$

*n* ≥ 361

Here, *Z*_*α*_ = 1.96, *Z*_*β*_ = 0.84, *P*_1_ = 0.08, *P*_2_ = 0.04 and *P*_1_ − *P*_2_ = 0.04.

Considering 10% dropout, the study will require recruiting approximately 396 participants for all the groups (*n* = 132 in each group) over a period of 16 months to adequately test the assumption.

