## Assignment of interventions: allocation

### Sequence generation {16a}

After inclusion in the trial, each prospective CS patient will be assigned either into the intervention (1% povidone iodine or chlorhexidine) or control (no-irrigation) group by using a block randomisation technique. A permuted block of six will be used to randomise the patients. A third party not related to the study will generate the permuted blocks and allocate the treatment in sealed opaque envelopes.

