## Oversight and monitoring

### Composition of the coordinating centre and trial steering committee {5d}

The trial will be conducted by the study research team, including the Goulburn Valley Health Obstetrics and Gynaecology Department and Goulburn Valley Health Research and Ethics Unit, in collaboration with the Obstetrics and Gynaecology Department staff. The principal investigator takes responsibility for supervision of the trial and ensures compliance with the study protocol. Vaginal cleansing prior to CS will be performed by the obstetrics and gynaecology study team clinicians. A third person with adequate clinical acumen independent to the project will assess the post-CS infection to reduce any potential bias, for example, the obstetrics and gynaecology consultant on call and obstetrics and gynaecology registrar. The statistical research plan and statistical analysis will be supervised by the Research and Ethics Unit, Goulburn Valley Health.

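### Letting each participant pick an envelope at random discards, on its natural reading, the order of the permuted blocks of six and leaves no sequence to check draws against

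*Protocol article*

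**What the plan says.** Four places in the protocol article describe the allocation.

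- Sequence generation {16a}: "A permuted block of six will be used to randomise the patients". The sequence and the envelopes come from outside the study: "A third party not related to the study will generate the permuted blocks and allocate the treatment in sealed opaque envelopes".
- Concealment mechanism {16b}: the envelopes are stored in the department, and "The envelopes will be not accessible to individuals directly involved in the study".
- Implementation {16c}: before delivery, "participants will pick one of the opaque sealed envelopes at random and pass it on to the treating team". The envelope is then opened and "the treating team will administer the allocation immediately prior to CS".
- Composition of the coordinating centre {5d}: "Vaginal cleansing prior to CS will be performed by the obstetrics and gynaecology study team clinicians".

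Trial design {8} gives the size: "A total of 396 eligible patients will be randomised in a 1:1:1 ratio". Who will be blinded {17a} names only the participants. No section states an order in which envelopes are used, or limits the pick to the current block.

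**The concern.** A permuted-block list does its work through its order. Each run of six must contain two of each arm, and this happens only if envelopes are taken in the sequence in which they were generated. If the woman picks from the stock, the third party's ordering has no effect. The method described under {16a} is then not the method that {16c} would produce. This is one stated rule defeating another, not a detail left out of a condensed article.

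Two things are at stake. The first is balance over calendar time, which protects the comparison if case mix or practice drifts during the 16 months and if recruitment stops short. The second is the ability to check the allocation. With a fixed order there is always one envelope that should come next, and a departure from it is visible. With a free pick there is none, and the clinicians who open the envelope know the arm.

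**Working it through.** **Inputs.** 396 randomised at 1:1:1 (Trial design {8}); block size 6 (Sequence generation {16a}); about 1200 deliveries a year, 25% by caesarean, over 16 months (Recruitment {15}); 375 women in the Abstract and Discussion. The article gives no figure for balance, so there is none to reproduce. Its total fits the design: 396/3 = 132 per arm and 396/6 = 66 blocks.

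**Envelopes used in block order.** An arm deviates from its target only inside an unfinished block. The worst cases are two of the first two (2 − 2/3 = 1.33) and none of the first four (0 − 4/3 = −1.33). The deviation therefore always stays below 2, and it is zero at the end of each block.

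**Envelopes picked at random from the whole stock.** The count in one arm after k draws is hypergeometric, with SD = √[k × (1/3) × (2/3) × (396 − k)/395].

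| k | Calculation | SD |
|---|---|---|
| 240 (assumed) | √(53.33 × 156/395) | 4.59 |
| 280 (assumed) | √(62.22 × 116/395) | 4.27 |
| 361 | √(80.22 × 35/395) | 2.67 |
| 375 | √(83.33 × 21/395) | 2.10 |
| 396 | √(88.00 × 0/395) | 0 |

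The counts 240 and 280 are assumptions about a trial that recruits short; they are not in the article. The figure 361 is its sample size before dropout, and 375 is its alternative total.

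**Gap between largest and smallest arm, by simulation.** Random picking gave a mean gap of 7.0 at 60 patients, 9.7 at 198 and 8.3 at 300 (95th percentiles 14, 19 and 16). In block order the gap never exceeded 2.

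**Chance that six consecutive women split 2:2:2.** With random picking it is C(132,2)³/C(396,6) = 0.125. For a completed block it is 1.

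**Would all 396 be used?** 0.25 × 1200 × 16/12 = 400 caesareans are expected in the recruitment period. Using every envelope needs 396/400 = 99% of them, before refusals and exclusions.

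**Effect on precision.** Take a large deviation at 280 draws: two arms of 85 and 101 instead of 93 and 93. The harmonic mean is 2 × 85 × 101/186 = 92.3, a loss of under 1%.

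**If the order were restored with blocks fixed at six.** A team that had seen the first five allocations would know the sixth, so at least 1 in 6 allocations would be predictable. The fifth would be known as well whenever the last two match, which has probability 3/15 = 1/5.

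**The case against.** The best defence is that {16c} speaks of picking one of the envelopes and does not say that the whole stock is on offer. A pick among the six envelopes of the current block would keep the blocking. That is possible, but nothing in the article says it, and such a pick would leave the last envelope of each block known to a team that had opened the other five.

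The rest of the defence limits how far the point can be taken. A reader might infer any of the following, and the article supports none of them:

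- *The allocation cannot be audited at all.* The article does not say that envelopes are unnumbered or draws unlogged, and the full protocol may cover this. What stands is narrower: a log would show which envelope a woman received, but not whether it was the one due, because a random pick makes none due.
- *The main safeguard against selective allocation is missing.* Opaque sealed envelopes, preparation by an unrelated third party, a draw made by the woman rather than a clinician, and outcome assessment by a person independent of the project are all stated.
- *The next allocation is predictable.* It is not under a random draw. Predictability arises only if a single block size is used in order, so it bears on the remedy. On the planned timeline the article could not have disclosed the block size during recruitment either: it appeared in March 2022, and recruitment was due to end in December 2021.
- *Concealment is flatly contradicted.* The rule under {16b} may concern study staff and stored envelopes before allocation, and it is unclear whether participants fall under it. This is an ambiguity to settle.

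**Conclusion.** The point holds as an inconsistency between stated steps. On its natural reading, {16c} turns the permuted blocks of {16a} into a simple random draw without replacement, and it fits poorly with {16b}. Randomness and unpredictability survive.

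What is lost is balance over time: an arm-size SD of about 4.3 to 4.6 if 240 to 280 envelopes are used, against a deviation below 2 in block order. That figure rests on two assumptions, the number used and a pick from the whole stock. Exact 1:1:1 returns only if all 396 are used, which is doubtful on the article's own caesarean numbers. The cost in power is trivial.

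The more important practical loss is that a repeated or discarded draw cannot be checked against a sequence, in a trial whose treating team knows the allocation. The point should be corrected, but it does not show that allocation was biased.

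**What to change.** If women are still to be randomised:

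1. Delete the random-pick step from {16c}.
2. Use sequentially numbered, opaque, sealed envelopes in strict numerical order, held and issued by someone outside the treating team.
3. Record participant number, date and time before the envelope is opened.
4. Vary the block sizes in multiples of 3 and keep them from the treating team, so that restoring the order does not make the end of each block predictable.
5. State under {16b} who may handle the envelopes, and when.

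This costs a few sentences of protocol text and a renumbered envelope set.

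If recruitment is complete, as the planned dates suggest, envelopes already drawn cannot be reordered. Then report the allocation as an unblocked random draw rather than as permuted blocks, unless records show that picks were confined to the current block, and reconcile {16a}, {16b} and {16c}. That costs only wording.

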## Assignment of interventions: blinding

### Who will be blinded {17a}

The participants will remain blinded to the interventions.

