#### Provisions for post-trial care {30}

All patients will return to standard care after the trial. All the patients included in the study will be followed up for a period of 28 days for the outcome signs and symptoms. We will follow up the patients telephonically on the 14th and 28th post-operative days and also during any hospital presentations or admissions until 28 days post-CS.

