### Outcomes {12}

#### Primary outcome

The primary outcome is endometritis: defined as tympanic temperature > 38 °C with uterine tenderness and/or foul-smelling vaginal discharge within 28 days of post-CS.

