#### Assessment of infection

A third person with adequate clinical acumen independent to the project will assess the post-CS infection to reduce any potential bias, for example, the obstetrics and gynaecology consultant on call and obstetrics and gynaecology registrar.

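### Only participants are stated to be blinded; the independent infection assessor is not masked to allocation, although endometritis and wound infection depend partly on clinical judgement

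*Protocol article*

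**What the plan says.** **Who is blinded.** Trial design {8} states: "This will be a single-centre, three-arm, single-blind, randomised controlled trial". Who will be blinded {17a} consists of one sentence: "The participants will remain blinded to the interventions".

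**Who knows the allocation.** Under Implementation {16c} the envelope is handed to the treating team and opened, and "the treating team will administer the allocation immediately prior to CS". The section on the coordinating centre and steering committee {5d} adds: "Vaginal cleansing prior to CS will be performed by the obstetrics and gynaecology study team clinicians".

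**Who judges the outcome.** Assessment of infection states: "A third person with adequate clinical acumen independent to the project will assess the post-CS infection". The stated aim is to limit bias, and the examples are "for example, the obstetrics and gynaecology consultant on call and obstetrics and gynaecology registrar". The same arrangement is repeated in {18a} and {5d}. None of the three places says whether this person knows the allocation.

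**What is judged.** The primary outcome, endometritis, is a tympanic temperature above 38 °C "with uterine tenderness and/or foul-smelling vaginal discharge within 28 days of post-CS". Wound infection, a secondary outcome, is a list of symptoms and signs at the incision. Neither definition has a laboratory criterion.

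**How follow-up is done.** Provisions for post-trial care {30} states: "We will follow up the patients telephonically on the 14th and 28th post-operative days", and adds any hospital presentation or admission up to day 28. Section {18a} repeats the telephone contacts but also refers to the same two days as visits.

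**The concern.** Independence from the project and masking to allocation are different safeguards. The first removes an interest in the result; the second removes the knowledge that could shape a borderline call. The protocol provides the first for its assessor and is silent on the second. Its example assessors come from the specialty that operates and cleanses, so followed as written it would allow a clinician who knows the allocation to decide whether a febrile woman has a tender uterus or offensive discharge, or whether a wound is infected.

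The control is no cleansing at all, which makes expectation plausible: an assessor who knows a woman was not cleansed may call a doubtful sign positive more readily. That would favour the antiseptic arms on the primary outcome and on wound infection.

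A lesser issue is follow-up after discharge. A telephone call cannot take a tympanic reading or elicit tenderness, and the article does not say how an infection reported only by telephone is judged against the definitions.

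**Working it through.** **1. Roles side by side**

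- Participant: stated to be blinded ({17a}).
- Treating team: knows the allocation, since it gives it after the envelope is opened ({16c}).
- Clinicians doing the cleansing: necessarily know it ({5d}).
- Infection assessor: independent of the project; knowledge of allocation not addressed (Assessment of infection, {18a}, {5d}).

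No sentence bars the assessor from having attended the caesarean or from reading its record.

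**2. Outcome components by openness to judgement**

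- Temperature above 38 °C: a measurement, always required for endometritis and sufficient for the fever outcome.
- Uterine tenderness: elicited at examination and judged.
- Offensive discharge: judged at examination or reported by the woman.
- Wound signs: judged, or partly reported by the woman.

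The temperature requirement limits the room for bias in endometritis but leaves the second component open. Wound infection has no measured component.

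**3. Size, as illustration only**

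The plan's own figure first (Sample size {14}): effect size = 0.04/√(0.08 × 0.92) = 0.1474; n = (2.80/0.1474)² = 360.64, so 361 as stated. The article then recruits 396, or 132 per group, allowing 10% dropout.

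- Analysed per arm: 132 × 0.9 = 118.8, about 119.
- Control events at 8%: 119 × 0.08 = 9.5.
- Antiseptic events at 4%: 119 × 0.04 = 4.8.
- Difference: about 4.8 women per arm. With the 125 per group given in the Abstract and Discussion it is 10 − 5 = 5.

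Reclassifying 2 to 3 women in one arm is 2/4.76 = 42% to 3/4.76 = 63% of that difference.

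What differential judgement could do, with assumed detection shares: suppose the true risk is 8% in both arms, all events are called in control, and a share s is called in an antiseptic arm. The apparent risk ratio is (0.08 × s)/0.08 = s, so 0.90, 0.80, 0.70 or 0.50 for s = 90%, 80%, 70% or 50%. In the other direction, suppose the true risk is 4% in both arms and 1% of uninfected controls are wrongly called infected. The control rate becomes 0.04 + 0.96 × 0.01 = 0.0496 and the ratio 0.04/0.0496 = 0.81; with 2% it is 0.04/0.0592 = 0.68.

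**4. Telephone follow-up**

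This is a separate mechanism. If a share of events is missed equally in all arms and there are no false calls, both counts fall and the ratio stays put. At an assumed 70% detection the counts are 9.5 × 0.7 = 6.7 and 4.8 × 0.7 = 3.3, ratio still 0.5. At 90% they are 8.6 and 4.3; at 50%, 4.8 and 2.4. The cost is events, and hence power.

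**The case against.** **The article does not hide its level of blinding.** It says single-blind and names the blinded party, so the word blinded in the title is not an error. That stands; the issue is the missing safeguard for the assessor.

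**Assessor and cleansing team are separate roles.** Section {5d} gives cleansing to study team clinicians and assessment to someone outside the project. A reader might infer that assessors do know the allocation or were at the operation. No sentence says so. What stands is that exposure is possible and not prevented.

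**The telephone gap is narrower than it looks.** A reader might infer that an infection treated by a GP cannot meet the primary definition and is counted as no event. The text does not support this. The definition does not say who takes the temperature or where. Tenderness is not required if offensive discharge is present, and a woman can report discharge by telephone. Section {18a} allows information to come from records, and hospital presentations to day 28 are followed. What remains is that no rule is given for telephone-only reports and that {18a} describes the contacts in two ways.

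**Call scripts and adjudication forms belong in a full protocol.** This is fair, and their absence is not the point. The article does answer who is blinded, and its answer leaves out the assessor.

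**Conclusion.** The point holds for assessor masking. The protocol plans an independent assessor to limit bias but does not mask that person, and the examples make knowledge of allocation plausible for outcomes that rest partly on judgement. This should be corrected.

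The likelihood, direction and amount of any bias cannot be derived from the document. The detection and false-call shares above are assumptions. The difference of about 5 women per arm shows only how few reclassifications would matter. It uses the overall post-caesarean infection rates of the sample size section, so it should not be read as a planned endometritis count; the article gives no endometritis rate.

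The telephone point is secondary. A reader might infer that telephone follow-up biases the comparison. Under-detection common to all arms lowers the event count but does not by itself distort the ratio. What needs correcting is the conflict between calls and visits in {18a} and the absence of a rule for telephone-only reports.

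**What to change.** **Main change.** Amend Who will be blinded {17a} and Assessment of infection, with matching wording in {18a} and {5d}, to state that the already-planned independent assessor is masked to allocation. That means the assessor:

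- was not present at the caesarean;
- does not open the envelope;
- judges outcomes from a symptom and examination form that omits allocation, with cleansing recorded on a separate sheet.

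**Secondary change.** In {18a}, settle whether the day 14 and 28 contacts are calls or visits. State that an infection reported only by telephone is checked against the existing primary and secondary outcome definitions using GP or hospital records. Any broader definition based on a clinician's diagnosis should be a sensitivity analysis only, so that the primary outcome is unchanged.

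**Cost.** Protocol wording, a separate sheet, record requests for positive calls, and some limit on which on-call clinician may assess a given woman. No extra assessor post is required. Trial status gives December 2021 as the planned end of recruitment, before the article appeared. For women already assessed, the report should therefore say who assessed them and whether that person knew the allocation.

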### Procedure for unblinding if needed {17b}

There should not be any need to unblind the participants. The allocated treatment in each arm is commonly utilised within standard practice, and the intervention materials are well known to the treating team. Nevertheless, if required, unblinding can be carried out by the study site investigators.

## Data collection and management

### Plans for assessment and collection of outcomes {18a}

A predeveloped questionnaire will be completed with patients’ socio-demographic characteristics and required clinical and pregnancy-related information. All the fever, infection and readmission-related information such as duration of artificial rupture of membrane/spontaneous rupture of membrane, duration of labour, BMI, gestational diabetes mellitus (GDM) with current diet or insulin regime, duration of surgery, estimated blood loss (EBL), previous CS (1/2/3) of elective/emergency nature and vaginal examination at CS will be completed from either the patients or their record or at follow-up visits on the 14th and 28th post-operative days. All the patients included in the study will be followed up for a period of 28 days for the outcome signs and symptoms. Participants will be followed up over the phone fortnightly, at day 14 and day 28 post-CS. Participants will also be followed up during hospital presentations or admissions until 28 days post-CS. A third person with adequate clinical acumen independent to the project will assess the post-CS infection (primary and secondary outcomes) to reduce any potential bias, for example, the obstetrics and gynaecology consultant on call and obstetrics and gynaecology registrar. No identifying information but the aggregated data will be used for the analysis and interpretation.

